### Participants

People with any diagnosis of cancer who are currently receiving treatment or within 2 years of completing treatment for cancer are eligible to participate. Exclusion criteria are applied to minimise risk of harm associated with program participation, these are: 1) neutropenia; 2) severe anaemia; 3) bone metastases; or 4) any musculoskeletal, cardiovascular or neurological disorder that could place the participant at risk of injury or illness resulting from the exercise program (as determined by the patient’s physician). No age restrictions are applied but people with cancer are required to obtain physician consent prior to participating in the Life Now Exercise program. Carers of eligible participants are permitted to concurrently attend the program.

Potential participants are required to self-enrol in the Life Now Exercise program by telephoning the Cancer Council Western Australia. Multiple approaches are adopted to raise awareness of the program including: education for oncology clinicians and support staff to facilitate direct referral of patients; distribution of program flyers at hospitals, cancer centres and community-based organisations as well as health professional and patient events; email and mail out communications to people who have contacted Cancer Council WA and expressed interest in exercise; advertisement and coverage in local media; and information provided on the Cancer Council Western Australia website and social media accounts. People with cancer who register are mailed an information package containing resources, screening documentation and contact details of the relevant program site. If the number of registrants exceeds the capacity of a site, participants are placed on a wait list for the next term of the program.

The program evaluation protocol was approved by the Edith Cowan University Human Research Ethics Committee (ID: 6192) and all participants involved in the evaluation provided written informed consent.

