### Evaluation

Evaluation of the Life Now Exercise program involves measures of uptake, safety, adherence and effectiveness of the program. These analyses incorporate elements of the RE-AIM (reach, effectiveness, adoption, implementation and maintenance) framework [31]. Evaluation of the effectiveness of the program involves comparisons among pre-program, post-program and 6 months follow-up assessments. The evaluation will be undertaken on a sample of 600 people with cancer participating in the program (refer sample size calculations below) with data collection initiating in 2011 and proceeding until the target sample size is achieved.

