#### Effectiveness-objective assessments

Objective measurements of physical function, resting blood pressure, height, weight, waist and hip circumferences occurs for all participants at pre- and post-program time points. Physical function is assessed using the 400 metre walk and repeated chair rise tests with lower time taken to complete the tests representing higher functional performance. As a measure of cardiovascular fitness, peak oxygen consumption (VO_2_peak) is estimated from the 400 metre walk test time and heart rate response [32]. A validated oscillometric device or sphygmomanometer is used to record resting brachial blood pressure. Circumferences are measured using a constant tension anthropometric tape in accordance to standard protocols. These assessments are performed in triplicate with the exception of the 400 metre walk test. These assessments are conducted by the same exercise physiologist administering the exercise intervention.

A sub-set of participants willing to attend a tertiary assessment centre complete additional objective assessments to evaluate further components of functional capacity [33]. Involvement in the additional assessments is open to any participant willing to attend an additional testing session and as such, evaluation of these endpoints will be exploratory. Maximal strength of the lower and upper body is determined using the 1RM in the leg press, chest press and seated row exercises. Usual and fast pace 6 metre walks evaluate ambulatory ability while the 6 metre backwards walk is used to assess dynamic balance. Static balance is determined using the sensory organisation test performed on a Neurocom Smart Balancemaster (Neurocom, OR, USA). Body composition and bone health are derived from dual-energy X-ray absorptiometry (DXA; Hologic Discovery A, MA, USA). Regional and whole body lean mass and fat mass as well as trunk adiposity, visceral fat and adipose indices are assessed using whole body DXA scans. Areal bone mineral density of the hip (total hip) and lumbar spine (L_2–4_) as well as whole body bone mineral content is measured by DXA using standard procedures. These assessments are conducted by an independent research assistant not involved with administering the exercise intervention.

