#### Statistical analyses

Data will be analysed using an intention-to-treat approach with maximum likelihood imputation of missing values. Analyses will include standard descriptive statistics, Student’s *t*-tests, chi-square, correlation, regression and repeated measures ANOVA (or ANCOVA as appropriate) to examine differences over time. Clinically relevant covariates will be included in analyses. Sub-group analyses based on cancer site and anti-cancer treatment status will be conducted. Investigations into responders and non-responders will be conducted to explore heterogeneity of intervention effect.

Sample size calculations were based on having sufficient power to detect a small effect (*d* = 0.02) in study endpoints. Given the number of planned assessments, correction for multiple testing is required. An alpha level of 0.001 was applied which provides adjustment for up to 50 tests. A priori, 420 participants are required to achieve 80% power at an alpha level of 0.001 (two tailed) to demonstrate a mean paired difference of *d* = 0.02 from pre- to post-program. To ensure sufficient participant numbers at the completion of the Life Now Exercise program, sample size calculations accounted for a 30% attrition rate. Thus the evaluation will be conducted on a sample size of 600 participants.

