
Information arising from the implementation of the Life Now Exercise program extends existing reports of community-based exercise programs for people with cancer designed for ongoing operation [46–49]. The ‘Livestrong at the YMCA’ program operates at over 400 sites throughout America [50]. The program involves 12 weeks of twice weekly group based exercise sessions administered at YMCA facilities by personal trainers and the benefits of participation have been reported on a sample of 187 participants [47]. The ‘FitSTEPS for Life’ program operates across various community based exercise sites (e.g., community centres, churches, health centres) in Texas, USA where people with cancer receive an individualised exercise plan and are provided access to ongoing exercise supervision [51]. Improvements in a range of quality of life domains were observed following 2 years of involvement in the program on a sample of 177 participants [46]. Cancer specific community-based exercise programs have also been developed in Canada. The ‘CanWell’ program is a 12-week exercise (two supervised sessions weekly) and education program administered by staff trained in program delivery at a YMCA facility in Ontario. Evaluation of a sample of 65 participants demonstrated improvements in quality of life and physical function at the completion of the program [49]. The BEAUTY program (*Breast* cancer patients *E*ngaging in *A*ctivity while *U*ndergoing *T*reatment) is a 12-week program involving twice weekly group based exercise sessions and biweekly education sessions delivered by certified exercise physiologists at a single tertiary exercise facility in Alberta [52]. Evaluation was undertaken on a sample of 80 patients which demonstrated safety but no clinically significant improvements following program completion (possibly associated with the low attendance rate of ~30%) [48]. These data provide promising initial evidence of the effectiveness of cancer specific exercise programs implemented in the community but significant continued effort is required to increase knowledge translation and implementation approaches. Evaluation of the Life Now Exercise program extends existing reports by assessing the effectiveness of a community-based exercise program in the largest sample of people with cancer to date (*n* = 600) using a comprehensive suite of assessments. The sample size and inclusive participant criterial allows for sub-group analyses which may provide insight into how people with different cancer types and treatment status respond to exercise. Importantly, examination of which participants do and don’t respond to exercise will provide novel information regarding demographic, clinical, motivational and other characteristics/factors that influence the response to exercise in people with cancer. Further to this, the evaluation will provide insight into what kind of participants engage in a community-based exercise program which may help inform future work to target people with cancer who require additional stimulus to engage in positive exercise behaviours. Examination of the cost-effectiveness of the program represents a unique addition to the literature and significant advance in current knowledge regarding the potential value of cancer-specific exercise interventions to the health system. Additionally, detailed reporting of the elements contributing to the design and implementation of the Life Now Exercise program may help inform the development of feasible, effective and sustainable supportive care exercise services. Collectively this information will help guide future research and translational work addressing the low levels of exercise behaviour in people with cancer.

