
There are important limitations to note in the design and evaluation of the Life Now Exercise program. As participants self-enrol into the program they will have a level of motivation to undertake exercise that may not be representative of all people with cancer. Integrating systematic referral of all people with cancer through oncology departments and treatment centres is not possible within the scope of this study. While program sites span metropolitan and regional areas, the program is implemented in Western Australia only and limited to the context of the Australian health care system. Program participation is funded by Cancer Council Western Australia so as to be delivered at no cost to people with cancer. These factors may limit the generalizability for implementation as an on-going program in other settings. Evaluation of the program is limited by the single-group design which precludes appraisal against a comparable sample of people with cancer. Evaluation is also limited by the reliance on community-based health professionals to administer assessments and return program documentation to the research team. Assessor bias cannot be ruled out as the same health professional who delivered the intervention administered the objective assessments (note: patient reported outcomes were conducted independently by the participant). The potential influence of social support on exercise motivation and behaviour may not be adequately assessed by domains of the Theory of Planned Behaviour questionnaire. These limitations are offset by strengths to the implementation and evaluation of the Life Now Exercise program. The program incorporates theory based behaviour change strategies and applies evidence based practice in the delivery of exercise to people with cancer. External validity of the program is supported by the implementation within a community-based setting to people with any diagnosis of cancer. This is further enhanced by administering the program as a “real-world” intervention delivered in a standard supportive care service setting. Evaluation of the program is guided by the RE-AIM framework and includes a robust suite of endpoints.

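### With one uncontrolled group and a single baseline, the planned responder analysis can describe who improved but cannot identify variation in the program's effect

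*Protocol article*

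**What the plan says.** The Statistical analyses section of the protocol article gives the responder analysis one stated purpose: "Investigations into responders and non-responders will be conducted to explore heterogeneity of intervention effect". No responder definition or cut-off appears there, which is acceptable in an article.

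The Discussion says that examining who does and does not respond will provide new information on "demographic, clinical, motivational and other characteristics/factors that influence the response to exercise in people with cancer".

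On design, the Evaluation section says that "Evaluation of the effectiveness of the program involves comparisons among pre-program, post-program and 6 months follow-up assessments". Objective testing "occurs for all participants at pre- and post-program time points" only. No control group, repeat baseline or untreated run-in is described. The Participants section states the entry rule: "People with any diagnosis of cancer who are currently receiving treatment or within 2 years of completing treatment for cancer are eligible to participate". The limitations paragraph of the Discussion concedes that "Evaluation of the program is limited by the single-group design which precludes appraisal against a comparable sample of people with cancer", but does not connect this to the responder analysis.

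**The concern.** Both statements about responders are about variation in a causal effect: for whom the program works, and what makes it work better. That needs some knowledge of how each kind of participant would have changed without the program, and a single group followed from one baseline supplies none.

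Four things are mixed in each change score: the program effect, natural recovery, regression to the mean, and measurement or day-to-day variation. Natural recovery matters here because some participants are still on treatment and others are up to two years past it, so change without the program plausibly differs between people.

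At stake is how the result will be used. Advice on which patients respond to exercise could be drawn from patterns that would appear even if the program did nothing, or did exactly the same for everyone.

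**Working it through.** The plan gives no figure of its own to reproduce on this point. The check asks what a responder split would show when there is nothing to find.

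**Assumed inputs (not in the documents).** Outcome SD 1 at both times, bivariate normal; pre-post correlation ρ from 0.5 to 0.9; responder means a gain of at least 0.5 baseline SD; no program effect and no natural change.

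**Inputs from the Statistical analyses section.** 420 completers; two-tailed alpha 0.001.

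**Step 1: overall responder rate.** The SD of change is √(2(1−ρ)), so P(responder) = 1 − Φ(0.5/√(2(1−ρ))).

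**Step 2: rate by the outcome's own baseline.** Given baseline y, change is normal with mean −(1−ρ)y and variance 1−ρ². Averaging P(change ≥ 0.5) over the lowest and highest quarters of y gives the last two columns.

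| ρ | SD of change | 0.5/SD | Responders | Worst quarter | Best quarter |
|---|---|---|---|---|---|
| 0.5 | 1.000 | 0.500 | 31% | 56% | 10% |
| 0.7 | 0.775 | 0.645 | 26% | 43% | 11% |
| 0.8 | 0.632 | 0.791 | 21% | 34% | 11% |
| 0.9 | 0.447 | 1.118 | 13% | 20% | 8% |

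**Step 3: the same effect for everyone.** Suppose instead that every participant gains 0.2 SD of the paired difference (an assumed value). Then Φ(−0.2) = 42% still show a change below zero. The worst-against-best quarter contrast is 64% v 15% at ρ = 0.5 and 26% v 11% at ρ = 0.9. There is no variation in effect here either.

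**Step 4: would the plan's alpha screen this out?** The correlation of baseline with change is −√((1−ρ)/2): −0.50, −0.39 and −0.22 at ρ = 0.5, 0.7 and 0.9. With 420 completers, power is approximately Φ(atanh|r|·√417 − 3.291). At ρ = 0.9 this is Φ(0.2275 × 20.42 − 3.291) = Φ(1.35) = 91%; at 0.5 and 0.7 it exceeds 99.9%. A test of baseline against change would usually be declared significant with no real variation in effect.

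**Step 5: how far the artefact reaches.** Take a two-level factor, split in equal halves, related to the stable part of the score and unrelated to its error. With no effect, simulation of 2 million participants at ρ = 0.7 gives responder rates of 26% in both groups. Regression to the mean therefore does not turn such a factor into a predictor of change.

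**Step 6: does adjusting for baseline cure the problem?** For the same factor, with baseline gap g, regressing the post value on baseline and factor gives the lower group a coefficient of −g(1−ρ)/(1−g²/4), although nothing happened:

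- ρ = 0.5, g = 0.56: −0.28/0.922 = −0.30 SD
- ρ = 0.7, g = 0.67: −0.201/0.888 = −0.23 SD
- ρ = 0.8, g = 0.71: −0.142/0.874 = −0.16 SD

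So the adjusted model can create a false association where the plain change comparison gives none. For the outcome's own baseline, the reverse holds: it is the change score that misleads. Neither analysis is safe alone in a non-randomised group.

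**The case against.** The best defence is that the single-group limit is openly disclosed, the responder analysis is worded as exploratory, and the subgroup sentence is hedged: "The sample size and inclusive participant criterial allows for sub-group analyses which may provide insight". The list of methods also includes ANCOVA and clinically relevant covariates. Much of this stands. The disclosure is real, and the subgroup sentence needs no correction on this ground. But exploration still needs a target that the data can identify; covariates do not replace a comparison group; and the sentence on factors that influence response carries no hedge.

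A second defence is replicate measurement: "These assessments are performed in triplicate with the exception of the 400 metre walk test". This reduces within-session error for some objective tests. It does not remove day-to-day variation or natural recovery, it leaves out the 400 metre walk, and no replication is described for the questionnaires.

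Three stronger readings are tempting and are not supported:

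- A reader might infer that any factor related to a poor baseline, such as treatment status or low motivation, will falsely predict response. Step 5 shows otherwise. The artefact attaches to the outcome's own baseline and to measures sharing its transient error. Treatment status has a different problem: natural recovery may differ between those on and off treatment.
- A reader might infer that the analysis will mainly recover error. That depends on reliability and on true variation in effect, neither of which the article gives.
- A reader might fault the power of the subgroup analyses. The plan states no subgroup power, and this would be a separate question.

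**Conclusion.** The point holds as a limit on interpretation. Describing who improved is legitimate. Reading it as variation in the program's effect, or as factors that influence response, is not supported by one group with one baseline.

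The size is illustrative: with no effect, 31% to 13% would be classed as responders, and the contrast across quarters of the outcome's own baseline would run from 56% v 10% to 20% v 8%. These figures rest on normality, a 0.5 SD cut and correlations of 0.5 to 0.9, all assumed. The identification problem does not depend on those values, and no choice of cut-off removes it. The missing responder definition is not part of the criticism.

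**What to change.** In the Statistical analyses section:

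1. Restate the aim as exploring predictors or correlates of pre-post change, not variation in the intervention effect.
2. Analyse change on its continuous scale, with estimates and intervals.
3. Report each factor's association both with and without adjustment for the outcome's own baseline, and say why both are shown.
4. Show any responder percentage beside the percentage expected from test-retest variation alone, stating the reliability used.

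In the Discussion, replace the wording that factors influence response with wording that they are associated with change during the program. Apply the single-group limitation explicitly to this analysis, and name differing natural recovery by treatment status as an alternative explanation.

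The cost is a few reworded sentences and a little more analysis, with no new data. The downside is a weaker claim.

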**Trial Registration:**

ACTRN12616001669482 (retrospectively registered 5 Dec 2016).

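### All outcomes are tested, unranked, at a flat 0.001; Holm's procedure over a defined pre-to-post family would keep error control and recover power

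*Protocol article*

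**What the plan says.** The Statistical analyses section gives the basis for the sample size: "Sample size calculations were based on having sufficient power to detect a small effect". It refers to the study's endpoints collectively and singles none out. It then says "Given the number of planned assessments, correction for multiple testing is required", and sets the level: "An alpha level of 0.001 was applied which provides adjustment for up to 50 tests". The calculation is tied to one contrast. It states "420 participants are required to achieve 80% power at an alpha level of 0.001 (two tailed" and describes the aim as "to demonstrate a mean paired difference of *d* = 0.02 from pre- to post-program".

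The Evaluation section is wider: "Evaluation of the effectiveness of the program involves comparisons among pre-program, post-program and 6 months follow-up assessments". It does not rank these comparisons.

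The assessment schedules differ. Under Effectiveness-objective assessments, the clinic measures are taken before and after the program only. Under Effectiveness-patient reported outcomes, the questionnaires are completed at all three time points. The only outcomes given a lower rank are those of the tertiary-centre sub-set, of which the article says "as such, evaluation of these endpoints will be exploratory".

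**The concern.** A fixed cut-off of 0.05/50 fits a family of exactly 50 equally important tests. The article defines no such family. The outcomes measured in everyone number 33-35 for the powered contrast and 59-62 if the 6-month changes are added. The cut-off is therefore stricter than needed for the first set and slightly too lenient for the second.

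A single-step cut-off also takes no advantage of results already found significant. If the program improves many of these outcomes, as it is meant to, that costs power on each of them. With no family and no order defined, the report would also present a long list of results of equal standing.

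**Working it through.** **Inputs.** From Statistical analyses: alpha 0.001, two-sided, 80% power, 420 completers, 30% attrition, 600 enrolled, printed d = 0.02. Outcomes and schedules come from the two Effectiveness sections.

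**1. The plan's own figures.**
- 0.05/50 = 0.001, as stated.
- 420/(1 − 0.30) = 600, as stated.
- n = ((z for two-sided 0.001 + z for 80% power)/d)² = ((3.291 + 0.842)/d)². With the printed d = 0.02 this is 42,687. With d = 0.20 it is 427 (433 by the exact noncentral t). So 420 fits d = 0.20 approximately and not d = 0.02. That discrepancy is a separate error. The rest of this check assumes d = 0.20.

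**2. Outcomes measured in all participants.**
- Objective, pre and post only: 400 metre walk, chair rise, estimated VO2peak, blood pressure (1 or 2), weight, waist, hip = 7-8.
- Patient-reported, all time points: SF-36 8, QLQ-C-30 8, FACIT-Fatigue 1, BSI-18 4, exercise level 1-2, Theory of Planned Behaviour 4 = 26-27.
- Pre-to-post changes: 7 + 26 = 33 to 8 + 27 = 35.
- All changes from baseline: 7 + 2×26 = 59 to 8 + 2×27 = 62.

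**3. Family-wise error at 0.001 per test (Bonferroni bound).**
- 33-35 tests: at most 0.033-0.035.
- 59-62 tests: at most 0.059-0.062, slightly above 0.05 and beyond the 50 tests allowed for.

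**4. Holm's first step.** 0.05/35 = 0.0014 and 0.05/33 = 0.0015, and every later step is more lenient. Any p-value at or below 0.001, and every smaller one, lies below its own step. So no result significant at 0.001 can be lost.

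**5. Power per outcome, n = 420, d = 0.20, normal approximation.** The expected z is 0.20 × √420 = 4.099.
- At 0.001: Φ(4.099 − 3.291) = Φ(0.808) = 0.79 (0.783 by noncentral t).
- At Holm's first step with 34 tests, 0.05/34 = 0.00147, critical value 3.180: Φ(0.919) = 0.82. This is the least that Holm gives.
- Full Holm, simulated with 34 tests, 27 of them with d = 0.20, correlation 0.5: average power about 0.88, against 0.79 at the fixed cut-off. The family-wise error on the 7 true nulls is about 0.03 against 0.006, both below 0.05.

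**The case against.** The strongest reply is that 0.001 is a deliberate, stated correction and that the study was sized to have 80% power at that level. Many endpoints under strict family-wise control is a recognised design, and a single-group pragmatic evaluation need not end in one pass/fail verdict. This is also a condensed article, and a full protocol or registry entry may name a primary outcome. All of this stands. The flat cut-off is not invalid. The point is only that the rule the article does state can be replaced by one that is never less powerful and still controls the error.

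Some stronger readings are tempting, and the documents do not support them.
- *The verdict depends on which outcome is picked, so two analysts could reach opposite conclusions.* Both analysts would obtain the same endpoint-by-endpoint results at 0.001, and a pre-to-post result picked afterwards is still protected by the 0.035 bound.
- *All 33-35 outcomes compete at two time points, and the time point is open.* The objective measures have no 6-month assessment, and the sample size is tied to the pre- to post-program change.
- *An outcome may have been promoted after its result was known.* Data collection began in 2011 and the trial was "retrospectively registered 5 Dec 2016", but nothing says that outcome data had been examined, and the registry record is not at hand.
- *The cure is one primary outcome at 0.05.* At n = 420 and d = 0.20 its power would be 98%. But if the choice were informed by data, the false-positive risk over 33-35 independent outcomes could reach 1 − 0.95³³ = 0.82 to 1 − 0.95³⁵ = 0.83, far worse than the present rule.

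**Conclusion.** The point holds as one of efficiency and structure. The article leaves 33-35 outcomes unranked and tests them at a cut-off stricter than the powered contrast requires. It does not show an inflated error rate for that contrast. Only when the 6-month changes are added does the bound pass 0.05, and then only to 0.059-0.062.

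The avoidable loss of power is about 3 percentage points per outcome at the least (0.79 against 0.82) and about 9 points when most outcomes truly improve (0.79 against 0.88). These figures assume d = 0.20, 420 independent completers and, for the larger one, correlation 0.5 and 27 real effects of equal size among 34 tests. The article gives neither the correlation nor the number of real effects, and the gain shrinks towards the lower figure when fewer effects are real. The outcome count depends on how blood pressure and the modified exercise questionnaire are scored.

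**What to change.** In Statistical analyses:
- Define the confirmatory family as the pre- to post-program changes in the outcomes measured in all participants, and list them.
- Test this family with Holm's step-down procedure at two-sided family-wise 0.05 in place of the fixed 0.001 cut-off.
- Treat the 6-month contrasts (26-27 patient-reported scores) as a separate secondary family, also tested with Holm.
- Label the sub-group and responder analyses exploratory, as is already done for the tertiary-centre measures.
- Name a single primary outcome tested at 0.05 only if the choice is documented as made without sight of outcome data.

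The cost is wording: no new participants, data or assessments. There are two downsides. Simultaneous confidence intervals that match Holm are less simple than Bonferroni intervals. Control is also within each family, so the bound over both together is 0.05 + 0.05 = 0.10, which is why the 6-month results should be reported as secondary.

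### The only multiplicity correction described is a fixed 0.001 per test; if that is also the decision rule, Holm's step-down gives the same familywise protection with equal or better power

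*Protocol article*

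**What the plan says.** Everything on this point is in the Statistical analyses section of the protocol article. Its first paragraph lists the methods (t-tests, chi-square, regression, repeated measures ANOVA or ANCOVA) and gives no significance level. The second paragraph, on sample size, says "Given the number of planned assessments, correction for multiple testing is required" and continues "An alpha level of 0.001 was applied which provides adjustment for up to 50 tests". It names no procedure and does not state the familywise level.

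The same threshold sizes the study: 420 evaluable participants for 80% power, two-sided, on a paired pre-to-post difference printed as d = 0.02. Further, "sample size calculations accounted for a 30% attrition rate", which leads to 600 enrolled.

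The article gives no count of the endpoints expected to change and no correlations between endpoints.

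**The concern.** A constant 0.05/m for every test is the simplest way to hold the familywise error at 0.05, but it is not the best of the simple ways. Holm's procedure compares the smallest p-value with 0.05/m, the next with 0.05/(m-1), and so on, stopping at the first failure. It needs no assumption about dependence and rejects everything that the fixed threshold rejects.

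If 0.001 governs the analysis, a true change whose p-value lies between 0.001 and its step-down threshold would be reported as not significant, with nothing gained in error control. Several endpoints may well change together. The patient-reported outcomes section measures related constructs on more than one scale, and the null hypothesis is no pre-to-post change in a single group. The number of true effects could therefore be large, which is the situation in which Holm gains most.

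**Working it through.** **Inputs from the Statistical analyses section:** per-test alpha 0.001 two-sided; up to 50 tests; 420 evaluable; 80% power; 30% attrition; 600 enrolled; d printed as 0.02.

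**Assumed, because the article does not give them:** the number of true effects (0 to 50), a common d for all of them, and equal correlation between tests (0 to 0.7).

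**1. The threshold.** 0.05/50 = 0.001 exactly. With 50 independent true nulls, the familywise error is 1 - (1 - 0.001)^50 = 0.0488. This is the single-step Bonferroni threshold for an implied familywise level of 0.05.

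**2. The plan's sample size.** For a paired mean, n = ((z for two-sided 0.001 + z for 80% power)/d)^2 = ((3.2905 + 0.8416)/d)^2.
- At the printed d = 0.02, n = 42,687, and power at 420 is about 0.2%. The figure of 420 does not reproduce.
- At d = 0.20, n = 427 (433 by the noncentral t). Power at 420 is 79.1% (78.3% by the noncentral t). The figure of 420 is close to this.
- 420/(1 - 0.30) = 600 reproduces.

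The calculation below therefore uses d = 0.20 as the value that 420 approximately fits. It is not the printed value.

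**3. Holm's thresholds for m = 50.** The k-th smallest p-value is compared with 0.05/(50 - k + 1): 0.05/50 = 0.0010 for the first, 0.05/26 = 0.0019 for the 25th, 0.05/11 = 0.0045 for the 40th, and 0.05 for the 50th. The thresholds loosen appreciably only after many rejections.

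**4. Gain in power.** This is a simulation of 50 two-sided z-tests at n = 420, with mean 0.20 × √420 = 4.10 for true effects and 40,000 replicates per setting. Power is the average per true effect. Power at fixed 0.001 is about 79% throughout. Entries are Holm minus fixed 0.001, in percentage points:

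| True effects of 50 | Correlation 0 | 0.3 | 0.5 | 0.7 |
|---|---|---|---|---|
| 1 | 0.0 | 0.0 | 0.0 | 0.0 |
| 5 | 0.5 | 0.5 | 0.5 | 0.4 |
| 10 | 1.3 | 1.1 | 1.1 | 1.0 |
| 20 | 3.0 | 2.6 | 2.5 | 2.3 |
| 25 | 4.0 | 3.6 | 3.3 | 3.1 |
| 40 | 8.3 | 7.3 | 6.6 | 6.0 |
| 50 | 15.6 | 12.6 | 11.0 | 9.4 |

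Holm rejected everything that fixed 0.001 rejected, and its familywise error stayed at or below 0.05.

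**5. Sensitivity to d** (independent tests, n = 420), gain in percentage points:

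| d | 25 true | 50 true |
|---|---|---|
| 0.02 (printed) | 0.0 | 0.0 |
| 0.10 | 0.3 | 0.7 |
| 0.15 | 2.7 | 7.6 |
| 0.20 | 4.0 | 15.6 |
| 0.25 | 1.2 | 3.3 |
| 0.30 | 0.1 | 0.2 |

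The gain peaks near d = 0.20. At 0.10, power is about 11% under either rule with 25 or 50 true effects. At 0.30 it is above 99%.

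**The case against.** **The text does not say that 0.001 is the decision rule.** The figure occurs only in the sample-size paragraph, and the analysis paragraph gives no level. Sizing at 0.001 is compatible with a later Holm analysis, and the analysis-stage procedure may be in a plan not shown. This stands as a condition on the point. It does not remove it: the article says correction is required, offers only a threshold that "provides adjustment for up to 50 tests", and describes no other. Reading it as the decision rule is natural, and one sentence would settle the matter.

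**A reader might infer that the plan gives up 4 to 16 points of power for each true effect.** The documents do not support that as a general loss. It needs d = 0.20 (not the printed value), 25 to 50 of the 50 hypotheses false at that same d, independent tests, and 420 completers for every test. The article supplies none of the first three. The tertiary-centre assessments (Effectiveness-objective assessments section) are exploratory and made on a volunteer subset, so 420 does not apply to them.

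**A reader might also infer that overlapping scales enlarge the gain.** Correlation as such shrinks it: with all 50 true, from 15.6 points at correlation 0 to 9.4 at 0.7. Overlap helps only if it means that more endpoints truly change.

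**A fixed threshold is simpler to run.** It is valid for any set of up to 50 tests, and results can be judged as they arrive, post-program and then at 6 months. Holm needs the p-values of the family together. This stands as a modest cost.

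**Conclusion.** The point holds in a conditional form. If 0.001 is the decision rule at analysis, it is dominated by Holm's step-down: equal familywise protection under any dependence and never less power. That part is a mathematical fact and rests on no assumption about effects or correlations.

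The size does rest on assumptions. With 50 tests, 420 completers and d = 0.20 for each true effect, the gain is about 0 to 1 point with 10 or fewer true effects, 3 to 4 with 25, and 9 to 16 with all 50. Within each range it is smaller when endpoints are correlated. It is close to nil for d = 0.1 or 0.3, and nil at the printed 0.02.

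This is an efficiency improvement. The documents give no ground for calling the threshold a failure of type I error control: 0.001 protects it. The mismatch between d = 0.02 and 420 participants is a separate and clearer error in the same section, and adopting Holm would not correct it.

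**What to change.** In the Statistical analyses section:
- Keep 0.001 in the sample-size paragraph, described as the worst-case threshold used for sizing.
- Add a sentence stating that the declared family of tests will be analysed with Holm's step-down at a familywise level of 0.05, with m fixed at 50 if the family is not enumerated.
- Report Holm-adjusted p-values, with ordinary 95% confidence intervals for all estimates.

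The cost is a short text change, one line of code and a decision on which tests form the family. No further participants are needed. There are two downsides. The p-values of the family must be assessed together, so if 6-month tests belong to it, the adjusted results wait for them. Holm also yields no simple simultaneous confidence intervals; the article mentions none for these comparisons, but a fuller plan might.
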